### Outcomes {12}

The primary efficacy outcome of this trial is usual pain intensity score (VAS, 100 scale) at 8 weeks (V4). For secondary outcomes, see Table 1. For the method of aggregation, all outcome measures will be analyzed as continuous variables using mean values with appropriate statistical comparisons between groups (For further detail, see Statistical Analysis).

Through interviews, demographic information, medical history, surgical history, and prior/concomitant medications will be collected. Physical examination will include measurements of height, weight, and a patella examination. A knee X-ray will be taken to assign a K-L grade [40], which is used to assess exclusion criteria for osteoarthritis.

The usual and worst pain intensity scores assess the average and peak knee pain experienced over the past week, respectively. Participants mark their pain level on a visual analog scale from 0 to 100, with values recorded and rounded to the nearest whole number [41].

To assess knee function, participants complete the anterior knee pain scale (Kujala score), 13-item self-report questionnaire [42], with a total score calculated from the responses. Quality of life is assessed via the EQ-5D-5L [43] questionnaire, recording the sum of scores across five questions and today’s health status score. Depression severity is evaluated using the Patient Health Questionnaire-9 (PHQ-9) [44], with a total score from nine questions, while pain catastrophizing is assessed using the Pain Catastrophizing Scale (PCS) [45], totaling scores from 13 questions. Participants also rate their perceived recovery level on a 0 to 6 scale [46].

All pain and questionnaire assessments are conducted as electronic patient-reported outcomes (ePRO). Participants use digital tools provided at the site, with data automatically transferred to the electronic case report form (eCRF). For visit 3, if conducted as a televisit, participants may complete the assessments remotely.

### Sample size {14}

The primary efficacy variable of this clinical trial is the intensity of usual pain over the past week at 8 weeks post-treatment initiation, aiming to assess whether the experimental group shows superior improvement compared to the control group. The hypothesis for the superiority test on the primary efficacy variable is as follows: $${H}_{0}: {\mu }_{t}={\mu }_{c} vs. {H}_{1}: {\mu }_{t}\ne {\mu }_{c}$$, where $${\mu }_{t}$$ represents the usual pain intensity at 8 weeks for the experimental group, and $${\upmu }_{\text{c}}$$ represents the same for the control group.

The sample size was calculated based on prior study of MORA Cure PFP (ClinicalTrials.gov., NCT05614583). In the exploratory clinical trial, the usual pain over the past week of full analysis set at 8 weeks post-treatment was 2.31 ± 1.49 for the experimental group and 3.18 ± 2.43 for the control group [35]. The calculated effect size (Cohen’s *d*) is as follows: $$d=\frac{{m}_{t}-{m}_{c}}{\sqrt{\left({s}_{t}^{2}+{s}_{c}^{2}\right)/2}}=\frac{2.31-3.18}{\sqrt{\left({1.49}^{2}+{2.43}^{2}\right)/2}}=-0.428$$, where $${m}_{t}$$ is mean of the experimental group, $${m}_{c}$$ is mean of the control group, $${s}_{t}$$ is standard deviation of the experimental group, and $${s}_{c}$$ is standard deviation of the control group [47]. Values were used up to the second decimal place, and the effect size was calculated without rounding.

Using an effect size of − 0.428, a Type I error of 0.05, and a power of 0.8, the formula for calculating the sample size per group is: $$n=\frac{2{\left({z}_{1-\alpha /2}+{z}_{1-\beta }\right)}^{2}}{{\left(d\right)}^{2}}=\frac{2{\left(1.960+0.842\right)}^{2}}{{\left(0.428\right)}^{2}}=86$$, where $$n$$ is required sample size per group (rounded up to the nearest whole number), $$\alpha$$ is Type I error, $$\upbeta$$ is Type II error (1 − power), and $$d$$ is effect size [47].

Considering a typical dropout rate of 10–30% for clinical trials involving digital services [48], a 20% dropout rate was assumed for this study. Adjusting for this dropout rate, the required sample size per group is calculated as: $${n}^{\text{'}}=86\times \frac{1}{1-r}=107.5$$, where *r* is the dropout rate (0.2). Thus, the target sample size is set at 216 participants in total, with 108 per group (Fig. 1).

### Recruitment {15}

Participant recruitment will be handled by the institution. The investigator may invite patients under their care to participate, or participants may be recruited through in-hospital posters or an internet page. In these cases, participants must visit the institution to complete the informed consent form and undergo an eligibility check. All recruitment methods will be implemented only after obtaining IRB approval.

### Criteria for discontinuing or modifying allocated interventions {11b}

Participants will be withdrawn from the trial if they receive unapproved medication, procedures, or treatments that could impact trial outcomes; fail to meet inclusion/exclusion criteria post-enrollment; are lost to follow-up; experience adverse events requiring withdrawal as determined by the investigator; request to discontinue (withdrawal of consent); or if the investigator deems their continued participation unsuitable for any other reason.

If a participant misses a visit, the investigator must make every effort to contact them, encourage attendance, confirm their well-being, and document the reason for absence. Withdrawn participants will be included in efficacy and safety evaluations unless a valid reason for exclusion exists. Modifications to the intervention are not allowed in this trial.

### Relevant concomitant care permitted or prohibited during the trial {11d}

During the clinical trial, participants may use acetaminophen 650 mg as a rescue medication if they experience intolerable pain. The investigator may prescribe this at visits. Participants already on pain medication before the trial are encouraged to switch to the rescue medication but may continue their existing one at the investigator’s discretion. From baseline (visit 2) to follow-up (visit 5), participants should ideally avoid pain medications within 24 h before each visit.

The following are prohibited from visit 1 to visit 5: intra-articular or knee injections (e.g., corticosteroids), arthroscopic surgery, corrective osteotomy, knee replacement, or any unapproved procedures or surgeries, opioid analgesics for pain, topical knee ointments or patches, unapproved joint pain medications or treatments, and high-impact physical activities.

### Provision for post-trial care {30d}

After completing or withdrawing from the clinical trial, participants may resume regular medical care as before. If an adverse device effect arises, they may be compensated for medical expenses per the compensation policy until the issue is resolved. The sponsor will secure IRB approval for the insurance policy covering such compensation. Additionally, if there is any suspicion of an adverse event after a participant’s trial completion or withdrawal, the investigator must assess and provide further medical care as needed.

Participants will not be able to continue accessing the app after the trial period ends. The investigational medical device will be deleted from participants’ mobile phones at V5 (end of trial period), as access to unapproved medical devices by study participants must be limited to the minimum necessary for the trial.

## Assignment of interventions: allocation

### Sequence generation {16a}

Only participants who meet the inclusion/exclusion criteria will be randomly assigned to either the experimental or control group in a 1:1 ratio. The method used for this assignment is computer-generated block randomization. To ensure independence, a third-party institution will be entrusted with generating the randomization list. Stratification will not be performed.

### Concealment mechanism {16b}

To conceal the randomization list, neither the sponsor nor the delegated CRO will have access to the list. The sequence will be generated within the third-party institution, and it will be directly built into the eCRF system. The results of this process will be encrypted and will not be identifiable.

### Implementation {16c}

Random assignment will be conducted through an interactive web response system (IWRS) incorporated into eCRF. The pre-generated randomization list will be embedded into the program.

## Assignment of interventions: blinding

### Who will be blinded {17a}

This clinical trial is open-label; therefore, blinding is not applicable.

Due to the nature of digital healthcare apps, complete blinding of participants and investigators is not feasible. Statistical analysis by the biostatistician will commence only after trial completion and proper verification of all data followed by database lock. (For further detail, See “Data management {19}”). The additional benefit of blinding the biostatistician is limited.

### Procedure for unblinding if needed {17b}

This clinical trial is open-label; therefore, blinding is not applicable.

## Data collection and management

### Plans for assessment and collection of outcomes {18a}

Source documents refer to all original records of clinical findings, observations, or other activities essential for the evaluation and replication of the clinical trial. Examples include, but are not limited to, medical records, clinical findings, knee X-rays for K-L grade evaluation, participant diaries for recording treatment compliance, and patient-reported outcomes collected via electronic devices (pain intensity, Kujala scale, EQ-5D-5L, PHQ-9, PCS, and overall perceived level of recovery). For the treatment group, compliance data from the application can also serve as source data.

Data collection and recording are performed by the investigator under the supervision of the principal investigator, electronic CRF as the primary method of data collection. The investigator must ensure the accuracy, completeness, legibility, and timeliness of the data included in the case reports and other records. Data recorded in the CRF must be consistent with the source documents; any discrepancies or omissions must be accompanied by an explanation. Changes to electronic CRFs must be traceable through an audit trail system.

### Plans to promote participant retention and complete follow-up {18b}

Participants will receive 50,000 won (equivalent to 26 US dollars) per visit as transportation reimbursement. If Visit 1 and Visit 2 are conducted simultaneously, participants will receive double the amount, and the same amount will be provided for Visit 3, even if it is an electronic visit. At each visit, the investigator will check and monitor the treatment progress (automated data from the app for the treatment group, patient diaries for the control group). The application includes a notification feature that allows reminders to be sent at the patient’s preferred time, and personalized messages are sent based on exercise compliance to help motivate the patient.

To meet regulatory requirements and ensure study integrity, data from participants who leave or are withdrawn from the trial will be collected, recorded, and retained for the period during which they participated in the study.

### Data management {19}

All clinical trial sites and investigators must ensure participant confidentiality and maintain accurate, legible, and timely records in compliance with regulations. The sponsor and regulatory authorities must be granted access to review records for monitoring, audits, and inspections. When using eCRF, authorized investigators enter data and automated systems detect discrepancies, issuing queries for corrections or confirmations. If IWRS or ePROs are used, data integration with the eCRF may occur.

The sponsor reviews the eCRFs for completeness and may issue queries for discrepancies or missing data, which the investigator must address. After the trial, protocol violations are determined, and once data integrity is confirmed, a database lock (DB lock) is performed, and a copy of the participant database is sent to the investigator. Statistical analyses take place post-DB lock.

The investigator and trial site must retain essential documents for a minimum of 3 years as required by country law, with the sponsor specifying the retention period. If further retention is unnecessary, the sponsor must inform the investigator and the clinical trial site in writing.

### Confidentiality {27}

The investigator must ensure the anonymity of study participants, avoiding any identification of participants’ names in documents submitted to the sponsor. Signed consent forms, source documents, and participant logs must be kept confidential and stored securely. All personal information collected through the investigational device follows personal information processing policy, and participants shall consent before installing the app.

Data collection systems in this trial comply with US code of federal regulation chapter 21, part 11 and local regulations. All data transmissions are encrypted, and access is controlled through individual user IDs and passwords, with only authorized and trained personnel permitted access.

### Plans for collection, laboratory evaluation, and storage of biological specimens for genetic or molecular analysis in this trial/future use {33}

Not applicable as no biological samples are to be collected.

## Statistical methods

### Definition of analysis sets

In this clinical trial, data will be analyzed using three sets: the full analysis set (FAS), the per protocol set (PPS), and the safety set. The FAS, aligned with the intention-to-treat (ITT) principle, will be the primary analysis set for efficacy evaluations, with additional analyses using the PPS. If discrepancies arise between the two, the outcomes will be presented and investigated. Safety evaluations will use the safety set.

The FAS includes participants who meet all of the following: have post-randomization primary efficacy data, records of applying the investigational device (test group) or performing self-exercise (control group), and were not improperly enrolled due to inclusion/exclusion violations. The PPS is a subset of the FAS, including those who completed the trial without major protocol violations, did not withdraw prematurely, and had an overall compliance rate of 50% or higher. The safety set includes all randomized participants with records of using the investigational device or performing self-exercise.

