**Fig. 2 Fig2:**
[figure not shown]
Multidisplicinary digital therapeutic app ‘MORA Cure PFP’ based on self-guided personalized exercise therapy and cognitive behavioral therapy for patellofemoral pain

For participants in the control group, a healthcare professional with experience in musculoskeletal disease treatment will conduct self-exercise education according to the paper-based self-guided exercise material. The exercise education will last for at least 15 min, and participants will be instructed to record the time spent on self-exercise in the patient diaries distributed at baseline. At each subsequent visit, participants will be asked to bring their ongoing diaries, and whenever feasible, the diaries will be collected to monitor their progress.

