### Strategies to improve adherence to interventions {11c}

To enhance adherence, participants are provided with education on the importance of treatment after group allocation. The experimental group receives instructions on using the application, while the control group is taught self-exercise using dedicated materials.

Each participant is required to perform daily self-treatment and log their activities, including exercise completion and duration. For the experimental group, the application automatically tracks and records exercise times, ensuring consistent monitoring. In the control group, participants manually log their exercise in a paper diary. During each visit, the investigator collects the diaries and monitors progress, offering support and feedback to encourage continued adherence.

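### The primary efficacy set is called ITT-aligned but excludes randomised participants on post-randomisation conditions, one of which is recorded differently in each arm

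*Protocol article*

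**What the plan says.** Under Definition of analysis sets, "The FAS, aligned with the intention-to-treat (ITT) principle, will be the primary analysis set for efficacy evaluations". A participant must meet every condition to enter it: post-randomisation primary efficacy data, plus "records of applying the investigational device (test group) or performing self-exercise (control group), and were not improperly enrolled due to inclusion/exclusion violations". The per-protocol set (PPS) is a subset of the FAS. The safety set carries the same record filter: "The safety set includes all randomized participants with records of using the investigational device or performing self-exercise". No efficacy set contains everyone randomised.

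The two arms generate records differently. Under Strategies to improve adherence {11c}, "the application automatically tracks and records exercise times" in the app arm, while controls log exercise by hand in a paper diary. Intervention description {11a} says of diaries at later visits that "whenever feasible, the diaries will be collected to monitor their progress". Section {11c} and Table 2 with its note 7 are firmer: diaries are reviewed and collected at visits, with return scheduled at V3, V4 and V5. Section {18a} names the diary as a source document for compliance.

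On missing data, section {20c} uses LOCF in the FAS but does not allow pre-treatment values to stand in for post-treatment ones. On timing, Data management {19} says "After the trial, protocol violations are determined", before database lock. The trial is open-label, and section {17a} adds that "The additional benefit of blinding the biostatistician is limited".

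**The concern.** Intention-to-treat protects the comparison because membership of the analysis cannot depend on what happens after allocation. Here it can. Participants know their arm, so whether they start the assigned activity, leave a trace of it, or provide a later pain score may all depend on allocation. The trace is automatic in one arm and needs a participant's effort in the other, so the same behaviour could count as a record in one arm and not in the other.

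This is a confirmatory superiority trial intended to support device approval and reimbursement. If its primary p-value comes from groups that randomisation no longer makes comparable, a result in either direction is open to challenge. The planned FAS-versus-PPS comparison cannot settle the matter, because both sets have already lost the same people. In the safety analysis, a control participant with an adverse event but no exercise record would leave both numerator and denominator.

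**Working it through.** **The plan's own figure.** From Sample size {14}: n = 2(1.960 + 0.842)² / 0.428² = 85.7, rounded up to 86 per group. Then 86 / (1 − 0.2) = 107.5, so 108 per group and 216 in total. This reproduces. The printed means and SDs give d = (2.31 − 3.18) / √[(1.49² + 2.43²)/2] = −0.87 / 2.016 = −0.432, close to the stated −0.428. The point does not depend on this difference.

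**The three conditions.**
- *Post-randomisation primary data*: known only after randomisation. Because section {20c} bars carrying baseline forward, imputation cannot bring back a participant with no post-treatment score.
- *Record of use or self-exercise*: known only after randomisation, and produced by different means in each arm.
- *No eligibility violation*: eligibility is a pre-randomisation fact, so this is the least harmful condition. Only its determination comes later, and no safeguard against knowing the arm is stated.

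**A concrete route.** Under Participant timeline {13}, V3 pain scores may be collected remotely by survey link, and Table 2 schedules the first diary return at V3. Suppose one participant from each arm completes a remote V3 and then stops. Both have a post-randomisation pain score. The app user has an automatic log, enters the FAS, and has the V3 score carried forward. The control's diary may never have reached the site. If the diary is the only record, that participant is left out. The plan assumes 20% dropout, so such cases are foreseeable.

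**Illustration of size.** The documents give neither the share excluded nor how those excluded differ, so both are assumptions:
- e = excess share of one arm excluded
- D = mean week-8 outcome of the excluded minus that of the retained, in SD units

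Working in SDs avoids assuming how the exploratory trial's scale maps onto the 0–100 VAS. With no true effect:
- bias = e × D
- SE = √[1/(108(1 − e)) + 1/108]
- type I error = Φ(−1.96 − bias/SE) + 1 − Φ(1.96 − bias/SE)

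| e | D | Bias (SD) | Share of planned effect (0.432) | Two-sided type I error |
|---|---|---|---|---|
| 5% | 0.25 | 0.013 | 2.9% | 5.1% |
| 5% | 0.5 | 0.025 | 5.8% | 5.4% |
| 5% | 1.0 | 0.050 | 11.6% | 6.5% |
| 10% | 0.25 | 0.025 | 5.8% | 5.4% |
| 10% | 0.5 | 0.050 | 11.6% | 6.5% |
| 10% | 1.0 | 0.100 | 23.2% | 11.0% |
| 20% | 0.25 | 0.050 | 11.6% | 6.4% |
| 20% | 0.5 | 0.100 | 23.2% | 10.7% |
| 20% | 1.0 | 0.200 | 46.3% | 28.3% |

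In the last row, SE = √(1/86.4 + 1/108) = 0.144, bias/SE = 1.386, and 1 − Φ(0.574) + Φ(−3.346) = 0.283.

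**Direction.** These rates count rejections either way. If the bias runs against the app, the chance of a false positive in the app's favour falls from 2.5% to Φ(−2.051) = 2.0% in the first row and Φ(−3.346) = 0.04% in the last.

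**Power if everyone is analysed.** Power = Φ(0.432 × (1 − f) × √(108/2) − 1.96), where f is the assumed share of the effect lost by keeping non-users. It is 88.7% at f = 0, 85.4% at 5%, 81.5% at 10% and 71.8% at 20%.

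**The case against.** The strongest reply is that the rule may exclude very few people. The definition asks for a record and does not name the diary or its return, so a reader who infers that a control must hand in a diary goes beyond the text. That reading has good support, because the diary is how controls log exercise and is a named compliance source, but another record might suffice. Collection is also better planned than the phrase in {11a} suggests, given {11c} and Table 2. All of this stands, and it limits the size of the problem. It does not remove the arm-specific condition.

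A reader might also infer that only the control arm is filtered, or that the bias favours the app. Neither is supported. App participants must install, register and start the plan, so non-starters are removed there too. If controls without a record are less diligent and in more pain, dropping them lowers the control mean and works against the app. If they stopped because they had recovered, it works the other way.

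Nor do the documents show that violations are judged by people who know the arm. Section {19} does not say who decides, and it already places the decision before database lock. What can be said is that no masking is described.

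Section {11b} keeps withdrawn participants in the evaluations unless there is a valid reason to exclude them. That term is undefined and does not override the FAS conditions. Finally, section {22} collects adverse events from consent for all but screening failures, so safety data are not lost. The fault lies in who is counted in the safety set.

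**Conclusion.** The point holds. The primary efficacy set is described as ITT-aligned but is not, because two of its conditions arise after randomisation and one is recorded differently by arm in an open-label trial. The set is fixed in the protocol text, so this is not detail left to an analysis plan. No planned analysis would expose the effect.

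The supportable strength is that the comparison can be biased, in an unknown direction and by an unknown amount. The illustrated range rests on assumed exclusion shares and outcome differences, exclusions in excess in one arm only, no other missing outcomes, and an unadjusted test. The planned baseline-adjusted ANCOVA could remove part of the bias if baseline pain explains the difference. With few exclusions the effect is negligible. A claim of a particular type I error, or of a bias towards the app, is not supported.

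**What to change.** - **Primary efficacy set:** all randomised participants, in the arm allocated, regardless of use records or eligibility deviations found later.
- **Missing outcomes:** state a likelihood-based or multiple-imputation method that uses baseline and keeps participants with no post-baseline score.
- **Current FAS:** report it as a sensitivity analysis, and define what counts as a record in each arm.
- **Safety set:** define it by provision of the app prescription or the exercise education at V2, not by a record of use.
- **Remaining exclusions (PPS):** decide them before database lock, as already planned, from listings that show neither arm nor outcome.

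**Cost.** This is mainly a change of wording, with no extra participants. Keeping non-users may dilute the effect: the power figures above stay above 80% for up to 10% dilution but fall to about 72% at 20%. They assume full outcome information on 108 per arm. Section {18b} collects withdrawn participants' data only for the time they took part, so the analysis will lean more on modelling, and the power figures are a ceiling. If only the 86 per arm left by the dropout allowance carry outcome information, undiluted power is 80.8%, and dilution would lower it further.
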